### Sample

3.5

The study will be conducted in an advanced hospital where approximately 9–12 stoma surgeries are performed monthly. The sample size was calculated using G*Power 3.1.9.2. The calculation was based on the primary outcome of the study, state anxiety. The effect size was calculated using the State Anxiety Inventory scores reported by Akbayrak and Uslu (2026), who evaluated the effect of preoperative stoma education including a wearable dummy stoma on postoperative stoma‐related anxiety, adjustment, and self‐efficacy. In that study, the mean State Anxiety Inventory scores were 36.24 ± 8.15 in the experimental group and 48.16 ± 10.14 in the control group. Based on these values, the effect size was calculated as *d* = 1.29. Using a two‐tailed independent‐samples *t* test, *α* = 0.05, power (1 − *β*) = 0.99, effect size = 1.29, and an allocation ratio of 1:1, the minimum required sample size was calculated as 46 participants, with 23 participants in each group. Considering a possible 10% attrition rate during follow‐up, including stoma closure, mortality, or participant withdrawal, the total planned sample size was increased to 52 participants, with 26 participants in each group.

### Randomization

3.6

Participants who meet the eligibility criteria and provide written informed consent will be randomly assigned to either the intervention group (*n* = 26) or the control group (*n* = 26) in a 1:1 allocation ratio. A computer‐generated block randomization method with a fixed block size of four will be used to ensure balanced allocation throughout the study.

The randomization sequence will be generated before participant recruitment by an independent researcher who will not be involved in participant recruitment, intervention delivery, outcome assessment, or data analysis.

To ensure allocation concealment, the group assignments will be placed in sequentially numbered, opaque, sealed envelopes prepared by the independent researcher. After participant enrolment and completion of baseline assessments, the intervention researcher will open the next envelope in sequence to determine group allocation. This procedure will be implemented to minimize selection bias and preserve the integrity of the randomization process.

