### Blinding

3.7

Owing to the nature of the intervention, the participants and the researcher performing the intervention cannot be blinded. However, outcome assessments will be performed by an independent researcher who is blinded to group allocation and is not involved in participant recruitment, randomization, or intervention delivery. Participants will be instructed not to disclose their group assignment during outcome assessments. In addition, an independent statistician blinded to group allocation will conduct the statistical analyses. The expert statistician will not be aware of the randomization sequence or group allocation and will not participate in the intervention implementation. The data obtained from the study will be recorded in the SPSS 21 program by the intervention researcher. Before statistical analysis, the intervention and control groups will be coded as Group A and Group B to maintain blinding. The expert who evaluates the study's data will not know which results belong to the intervention or the control group. He/she will share the study results with the researchers, for example, group A and group B results. Therefore, the study will incorporate blinded outcome assessment and blinded data analysis to minimize detection bias.

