
#### Control Group

3.8.3

As in the intervention group, patients who meet the criteria will be reported to the researchers by the stoma care nurse. The researcher will inform patients, and written informed consent will be obtained. One day before surgery, patients' state and trait anxiety levels will be evaluated. In addition, stoma adaptation of the patients will be evaluated at the time of discharge and 1 month after surgery. Patients in the control group will receive routine preoperative care and standard stoma training provided by a clinical nurse and a stoma care nurse. No additional stoma simulation procedure will be performed in this group.

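### A fixed, published block size of four, with envelopes opened by the unblinded intervention researcher, lets about one third of allocations be deduced in advance if that person also recruits

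*Protocol article*

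**What the plan says.** All references are to the protocol article.

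- **Randomization (3.6).** Allocation is "in a 1:1 allocation ratio" using a "block randomization method with a fixed block size of four will be used to ensure balanced allocation throughout the study". No stratification is mentioned. A researcher with no other trial role generates the list before recruitment. Concealment relies on "sequentially numbered, opaque, sealed envelopes prepared by the independent researcher". The timing is "After participant enrolment and completion of baseline assessments", at which point "the intervention researcher will open the next envelope in sequence to determine group allocation".
- **Blinding (3.7).** It concedes that "the participants and the researcher performing the intervention cannot be blinded". The outcome assessor is declared separate from recruitment, randomization and delivery. No such statement is made for the person who opens the envelopes.
- **Intervention Group (3.8.2).** The stoma care nurse refers eligible patients to the researcher who applies the simulation. The researcher then informs the patient, handles consent and measures baseline state and trait anxiety.
- **Control Group (3.8.3).** "The researcher will inform patients, and written informed consent will be obtained"; which researcher is not specified.
- **Inclusion Procedure (3.3).** Ward and stoma nurses identify patients and bring them to the researchers, in the plural.
- **Sample (3.5) and Limitations (5).** "the total planned sample size was increased to 52 participants, with 26 participants in each group", all from a single hospital.

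**The concern.** Sealed envelopes stop someone from reading the next assignment. They do not stop someone from working it out from earlier ones. With a known block of four, the last assignment in each block is determined, and so are the last two when the first two match. The person opening the envelopes sees every assignment in the only sequence, and the block size is printed in the article.

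If that person also decides whom to approach, or how firmly to encourage consent, the next assignment may be known during that conversation. Patients who seem more anxious or less likely to cope could then be steered, knowingly or not, towards or away from an arm. State anxiety and stoma adaptation are both self-reported and related to such traits. If the same researcher takes the baseline state anxiety score, as Intervention Group suggests, foreknowledge could also colour one of the two time points in the primary repeated-measures analysis.

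**Working it through.** **Inputs.** Block size 4, ratio 1:1 and the envelope procedure (Randomization); N = 52, 26 per arm (Sample); one centre (Limitations). The article gives no figure for predictability, so there is none to reproduce. Its total does fit its block size: 52 / 4 = 13 complete blocks, giving 26:26.

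**Assumption.** The person approaching patients knows the block size and remembers all earlier allocations.

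**Certain allocations, block of 4.** A block holds two of each arm, in 6 equally likely orders: AABB, ABAB, ABBA, BBAA, BABA, BAAB. An allocation is certain once one arm's two places are used up.

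| Position | Probability that it is certain | Probability that the best guess is right |
|---|---|---|
| 1 | 0 | 1/2 |
| 2 | 0 | 2/3 |
| 3 | 1/3 (first two match) | 1/3 × 1 + 2/3 × 1/2 = 2/3 |
| 4 | 1 | 1 |
| Sum | 4/3 | 17/6 |

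- Share certain: (4/3) / 4 = 1/3, that is 8 of the 24 positions.
- Over 13 blocks: 13 × 4/3 = 17.3 of 52 expected, with a minimum of 13 × 1 = 13 and a maximum of 13 × 2 = 26.
- Best guess (always the arm with more places left): (17/6) / 4 = 17/24 = 70.8%, or 36.8 of 52, against 50%, or 26 of 52, with no information.

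**Mixed, undisclosed blocks.** These were simulated with an observer who knows only which sizes are possible and updates after each allocation.

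| Scheme | Certain | Best guess right |
|---|---|---|
| Fixed 4 | 33.3% (17.3 of 52) | 70.8% |
| Sizes 4 and 6 drawn at random | about 5.6% (about 3 of 52) | 69.0% |
| Four 4s and six 6s in random order | about 7% (3 to 4 of 52) | about 69% |
| Sizes 4, 6 and 8 drawn at random | about 2.4% (about 1 of 52) | 67.7% |

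The four-and-six scheme fills the sample exactly: 4 × 4 + 6 × 6 = 52, with 4 × 2 + 6 × 3 = 26 per arm. The largest imbalance inside a block is 6 / 2 = 3 instead of 4 / 2 = 2.

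**Room for discretion.** Sample gives 9–12 stoma surgeries a month. Over the 12-month recruitment window (Trial Status) that is 12 × 9 = 108 to 12 × 12 = 144 surgeries for 52 places. Many patients will be ineligible, so this is an upper bound on choice, but enrolment need not be consecutive.

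**The case against.** The strongest reply is that the harmful link is not written down. Only the envelope opener is named as the intervention researcher. Recruitment is attributed to the researcher or the researchers, and nurses do the case-finding. The simulation is tied to the day before surgery, so there is little control over the order in which patients arrive. The standard safeguards are otherwise present: independent generation, opaque numbered envelopes, and opening only after enrolment and baseline.

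Much of this stands. The overlap of roles is strongly implied by Intervention Group but not stated, so the one-third figure is conditional. Limited control over arrival order narrows the opportunity, but does not remove it: whom to approach and how consent is discussed remain open. Opening the envelope late does not help if its content could already be deduced.

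Two stronger readings are tempting, and the article supports neither. A reader might infer that concealment has failed or that the trial will be biased; the calculation shows predictability, not its use. A reader might also infer that nothing could be done in the analysis. Baseline state and trait anxiety are measured before the envelope is opened and are listed as potential covariates (Evaluation of the Data), and baseline state anxiety is itself in the primary model. Selection through measured anxiety can therefore be partly addressed. Selection on unmeasured features, such as expected coping, cannot.

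**Conclusion.** The point holds as a weakness in a stated design choice. It is neither a contradiction nor a miscalculation, and the sample size is unaffected. If one person opens the envelopes, recruits, knows the block size and tracks allocations, an expected 17 of 52 assignments are known beforehand and a best guess is right 71% of the time. The arithmetic is exact. That the roles overlap is a likely reading of the article, and whether any bias would follow, or how large it would be, cannot be determined from it. The remedy is nearly free before recruitment, which makes the change worth making.

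**What to change.** 1. Before recruitment, have the independent researcher generate the list in randomly ordered blocks of 4 and 6, for example four 4s and six 6s. Replace the fixed size in Randomization with a statement that block sizes vary and are withheld from recruiting staff until enrolment ends. The published size of four should no longer apply.
2. Where existing roles allow, have the independent researcher hold the allocations and release each one only after consent and baseline measurement are recorded as complete.
3. State in Randomization who approaches and consents patients, and whether that person knows past allocations. Step 2 secures the order of events, but an intervention researcher who recruits will still learn each allocation by delivering it. The remaining 69% guessing rate falls only if approach and consent are kept apart from that knowledge.

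**Cost.** One regenerated list and a few changed sentences; a temporary imbalance of up to 3 instead of 2 within a block, with 26:26 kept at the end. Step 2 needs the independent researcher to be reachable when each patient is enrolled, the day before surgery. At 9–12 surgeries a month this is a small load.

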### Blinding

3.7

Owing to the nature of the intervention, the participants and the researcher performing the intervention cannot be blinded. However, outcome assessments will be performed by an independent researcher who is blinded to group allocation and is not involved in participant recruitment, randomization, or intervention delivery. Participants will be instructed not to disclose their group assignment during outcome assessments. In addition, an independent statistician blinded to group allocation will conduct the statistical analyses. The expert statistician will not be aware of the randomization sequence or group allocation and will not participate in the intervention implementation. The data obtained from the study will be recorded in the SPSS 21 program by the intervention researcher. Before statistical analysis, the intervention and control groups will be coded as Group A and Group B to maintain blinding. The expert who evaluates the study's data will not know which results belong to the intervention or the control group. He/she will share the study results with the researchers, for example, group A and group B results. Therefore, the study will incorporate blinded outcome assessment and blinded data analysis to minimize detection bias.

### Intervention

3.8

#### Preparation for Simulation Application

3.8.1

Preparation for simulation implementation is critical to the success of this study. At this stage, preparations are required to implement the simulation effectively. First, the goals and purpose of the simulation should be determined. Stoma simulation aims to enable patients to understand the surgical process and postoperative stoma care, reduce their anxiety levels, and accelerate the postoperative adaptation process.

For this reason, the materials to be used in the simulation will be carefully selected and prepared 1 day before surgery.

Since the patients used a two‐piece stoma bag in the long term, this material will be used in the simulation application. In addition, transparent stoma bags will be used because patients use them in the early postoperative period, and they will be familiar with the contents of the stoma. Coloplast products will be used according to the clinical protocol. The ‘Alterna Base Plate’ will be used for the stoma adapter and the ‘Alterna 2‐Piece, Drainable Bag’ will be used for the stoma bag. In addition, ‘Coloplast Paste’ will be used at the mouth of the stoma adapter. Care will be taken to use every product that should be used while providing routine stoma care while the stoma bag is sticking to the patient. This is a good opportunity for patients to see and familiarize themselves with the products used closely. To make the stoma bag realistic, soaked, reshaped napkins and tap water will be placed inside the bag. The amount of water will be 40 cc. The soaked napkins will be weighed with a precision scale, as equal amounts are desired for each patient. The weight of the soaked napkins will be 50 g. In the study aiming at stoma practice, it is seen that only tap water was placed in the bag (Karaveli and Demirarslan 2021). However, in this study, since patients who will open colostomy and ileostomy will be included, the content in the bag will be prepared in a more solid form. For this reason, both napkins and water will be placed in the bag. The weight of the stoma bag is 13 g. The napkins will also be dyed with ‘batikon’ to make the contents of the stoma bag resemble stool. The preparation stages of the stoma simulation are presented in Figure 2. Thus, as the duration of use increases, it will be indistinguishable from a real stoma and a stoma bag. ‘Brava Adhesive Remover, spray’ and ‘Brava Adhesive Remover, wipes’ will also be used when removing the stoma bag. This removes all paste residues and reduces skin peeling and skin damage. It will also increase comfort by reducing the degree of discomfort experienced by patients.

**FIGURE 2 nop270682-fig-0002:**
[figure not shown]
Preparation stages of the stoma simulation.

#### Intervention Group

3.8.2

The stoma care nurse will inform the researcher, who will perform the application of the patients who meet the study criteria. In addition, the stoma care nurse will mark the area where the stoma will be opened with a surgical skin marking pen that is nontoxic, iodine‐free, resistant to rubbing, easy to dry, and suitable for surgical interventions. In addition to routine preoperative care and standard stoma education, patients in the intervention group will receive a stoma simulation intervention. Throughout the study, potential side effects related to the intervention (such as skin irritation, physical discomfort, or psychological distress) will be monitored. If any adverse events occur, the participant will be evaluated by the clinical team, and appropriate support will be provided when necessary. All adverse events will be recorded and reported by the researchers. If serious physical or psychological adverse events related to the intervention are observed, the participant's involvement in the intervention will be discontinued, and the study process will be re‐evaluated by the researchers. For the patients in the intervention group, the researcher will measure their state and trait anxiety levels after informing them about the study and providing written informed consent. A preprepared stoma bag containing wet napkins (information about the contents will be given but not shown to the patients) will be attached to the patient. When the stoma bag is attached to the patient, care will be taken to ensure that it is in the area marked by the stoma nurse. The adapter will be cut into an estimated stoma size, heated by friction of the hands, and adapted to the skin by applying stoma paste. The patient will be asked to put his/her hand on the adapter and apply pressure. Then, the stoma bag is filled with napkins and water, and the adapter will be combined. The patient will be informed that he/she should not hesitate to perform any activity with the stoma bag for 24 h. The patient will be allowed to go to the toilet, eat, sleep, and perform all daily activities with the stoma bag. Brava Adhesive Remover, spray, and Brava Adhesive Remover wipes will be used to clean the adapter adhesives and stoma paste residues on the morning of surgery. The patient's state of anxiety will be measured after the removal of the stoma bag. During the adaptation and removal of the stoma bag to the skin, the steps described in the literature will be followed (American Cancer Society 2019; Kirkland‐Kyhn et al. 2018). It may take time for patients who have had a stoma to adapt. Long‐term follow‐up is necessary for the study results to be more effective. In the literature, evaluating stoma adaptation in patients approximately 1 month after surgery is considered appropriate (Taylan and Aksoy 2021; Zhang et al. 2019; Whiteley et al. 2024). For this reason, stoma adaptations of patients will be evaluated at the time of discharge and 1 month after surgery. If patients have a possible problem with the stoma bag at night before surgery or have questions they want to ask, the information of the 24/7 open phone number where they can contact the researchers will be shared.

#### Control Group

3.8.3

As in the intervention group, patients who meet the criteria will be reported to the researchers by the stoma care nurse. The researcher will inform patients, and written informed consent will be obtained. One day before surgery, patients' state and trait anxiety levels will be evaluated. In addition, stoma adaptation of the patients will be evaluated at the time of discharge and 1 month after surgery. Patients in the control group will receive routine preoperative care and standard stoma training provided by a clinical nurse and a stoma care nurse. No additional stoma simulation procedure will be performed in this group.

### Data Collection

3.9

The data of the study will be collected with the ‘Patient Information Form’, ‘Spielberg State‐Trait Anxiety Scale’ and ‘Adaptation Scale for Individuals with Ostomy’ prepared by the researchers in light of the literature. Before stoma surgery, patients who meet the inclusion criteria will be interviewed and informed about the study. Patients who give verbal and written consent to participate in the study will be included. The ‘Patient Information Form’ and ‘Spielberg State‐Trait Anxiety Scale’ will be applied to the patients 24 h before stoma surgery. The ‘Spielberg State Anxiety Scale’ will be applied on the morning of surgery. The ‘Adaptation Scale for Individuals with Ostomy’ will be applied at discharge and 1 month after surgery (Table 1). The questions in the data collection form will be applied with a face‐to‐face interview technique. Each interview is expected to last approximately 15–20 min. Data will be collected in patient rooms to make patients feel comfortable. During the follow‐up to be performed in the first month after surgery, patients are called to the physician's control in accordance with the hospital protocol. After physician control, the researcher will have a face‐to‐face interview with the patients in the stoma nurse's room and evaluate the stoma adaptation.

**TABLE 1 nop270682-tbl-0001:** Participant timeline: Schedule of enrollment, interventions and assessments.^a^

Timepoint^b^	Trial period					
	Enrollment		Post‐randomization			Close out
	−*t* _ *i* _ to 0	0	*t* _1_ (24 h before surgery)	*t* _2_ (surgery morning)	*t* _3_ (discharge)	*t* _4_ (1 month ±7 days)
Enrollment						
Eligibility screen	X					
Informed consent	X					
[Baseline demographic data]	X					
Randomization		X				
Intervention/comparator						
[Stoma simulation]^c^			X	X (removal)		
[Control]^d^						
Assessments						
[STAI‐trait anxiety]	X			X		
[STAI‐state anxiety]	X			X		
[Ostomy Adjustment Inventory]					X	X

^a^
Recommended content can be displayed using various schematic formats.

^b^
List target timepoints and acceptable time windows in this row (e.g., 30 ± 3 days).

^c^
Arrow indicates continuous delivery of intervention (e.g., drug).

^d^
Example illustrates delivery of comparator at discrete timepoints (e.g., psychotherapy).

### Data Collection Tools

3.10

#### Patient Information Form

3.10.1

This form was prepared by researchers on the basis of the literature (Diniz et al. 2023; Taylan and Aksoy 2021; Xavier et al. 2024). It includes individual factors (control variables) that will affect stoma adaptation. It consists of nine questions, including the patient's age, gender, medical diagnosis, and stoma‐related characteristics, such as placement and type.

#### Spielberg State‐Trait Anxiety Scale

3.10.2

The scale was developed by Spielberger et al. (1970), and its Turkish validity and reliability study was conducted by Öner and Le Compte (1983). The scale consists of two separate dimensions, namely, state anxiety (STAI‐I) and trait anxiety (STAI‐II), and these dimensions aim to measure the anxiety states of individuals in different contexts. State anxiety measures the transient anxiety that an individual feels at a specific moment and in a specific situation and can be influenced by environmental factors, immediate stressors, or specific events. The anxiety felt by the patient before surgery is assessed with this dimension. The questions aim to understand the level of anxiety, tension and restlessness the person feels in the current situation. Trait anxiety is the individual's level of predisposition to anxiety in general. It is more closely related to an individual's personality traits and refers to a more prolonged state. The fact that a person usually has an anxious personality in daily life is evaluated with this dimension. It aims to understand how the individual reacts to anxiety and stressful situations in general. In this study, the anxiety scale will be used to assess the anxiety levels experienced by individuals who will undergo stoma surgery in a specific situation or continuously (Karaveli Çakır and Özbayır 2018; Öner and Le Compte 1983; Spielberger et al. 1970).

The scale consists of 40 items; 20 items measure state anxiety and the other 20 measure trait anxiety. The scale items are 4‐point Likert‐type. Responses range from ‘Never’ (1) to ‘Very often’ (4). The state anxiety scale includes 10 inverse statements (1, 2, 5, 8, 11, 15, 16, 19, 20) and 10 straight statements, whereas the trait anxiety scale includes 7 inverse statements (21, 26, 27, 30, 33, 36, 39) and 13 straight statements. Inverted statements represent positive emotions, and straight statements represent negative emotions. Although the scores of the inverse statements are evaluated by transforming them, the scores of the straight statements are used directly. Both scales are scored between 20 and 80, and the higher the score is, the higher the anxiety level. In the validity and reliability study, the Cronbach's alpha (*α*) coefficient value was between 0.94 and 0.96 for the STAI‐I and between 0.83 and 0.87 for the STAI‐II (Öner and Le Compte 1983).

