### Evaluation of the Data

3.11

The data obtained from the study will be analysed using SPSS 21 (Statistical Package for the Social Sciences) software. First, the demographic and clinical characteristics of the participants will be summarized using descriptive statistics (frequencies, percentages, means and standard deviations). To assess baseline comparability between groups, independent‐samples *t* test will be used for normally distributed continuous variables, Mann–Whitney *U* tests for non‐normally distributed continuous variables, and chi‐square tests for categorical variables.

The primary outcome of the study is state anxiety measured using the State Anxiety Inventory. Changes in state anxiety scores between the intervention and control groups over time will be evaluated using repeated‐measures analysis of variance (ANOVA), including group, time, and group‐time interaction effects. The secondary outcome of the study is postoperative stoma adaptation measured using the Ostomy Adjustment Inventory. Changes in stoma adaptation scores between groups and across follow‐up measurements will also be evaluated using repeated‐measures ANOVA.

Age, gender, diagnosis, stoma type, baseline trait anxiety scores and baseline state anxiety scores will be prespecified as potential covariates. Baseline comparability between groups will be assessed, and adjusted analyses will be performed where clinically relevant imbalances are identified.

All primary analyses will be conducted according to the intention‐to‐treat (ITT) principle. Missing outcome data will be handled using multiple imputation methods. In addition, a per‐protocol analysis including participants who complete all planned assessments will be conducted as a sensitivity analysis. A significance level of *p* < 0.05 will be accepted in all analyses.

Every effort will be made to minimize missing data throughout the study. Reasons for missing data, participant withdrawals, mortality, and stoma closure will be documented and reported in detail. Results will be reported with 95% confidence intervals, effect sizes, and *p* values. The clinical significance of the findings will also be emphasized.

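### The state-anxiety scoring key states 10 reverse-scored items but lists nine; coded as printed, it would leave one item of the primary outcome unreversed

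*Protocol article*

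**What the plan says.** Section 3.10.2 (Spielberg State‐Trait Anxiety Scale) sets out the instrument: "The scale consists of 40 items; 20 items measure state anxiety and the other 20 measure trait anxiety". For the state part it says: "The state anxiety scale includes 10 inverse statements (1, 2, 5, 8, 11, 15, 16, 19, 20) and 10 straight statements". For the trait part it gives "7 inverse statements (21, 26, 27, 30, 33, 36, 39) and 13 straight statements". It adds that inverse items express positive emotions and straight items negative ones, and that "the scores of the inverse statements are evaluated by transforming them, the scores of the straight statements are used directly". On range and direction: "Both scales are scored between 20 and 80, and the higher the score is, the higher the anxiety level".

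Section 3.11 (Evaluation of the Data) makes this score the primary endpoint: "The primary outcome of the study is state anxiety measured using the State Anxiety Inventory". The same section promises results with 95% confidence intervals and effect sizes, and a discussion of clinical significance.

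**The concern.** The sentence contradicts itself. It announces ten reverse-scored state items and then names nine. Every item outside the list counts as straight and enters the total as recorded. A programmer who codes the list literally would therefore let one item that expresses a positive emotion add to the anxiety score.

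What is at stake is the scale on which the primary result is reported. Point differences and their confidence limits would be too small, and a calm or anxious patient would not reach the end of the scale that the article describes. Someone who receives only total scores would have difficulty noticing. A minimum and maximum check on the totals would not catch it either, because every item still contributes 1 to 4 and no total leaves 20 to 80.

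**Working it through.** **1. Count the keys**

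| Key | Stated inverse | Listed inverse | Straight implied by the list | Straight stated |
|---|---|---|---|---|
| State anxiety (3.10.2) | 10 | 9 (1, 2, 5, 8, 11, 15, 16, 19, 20) | 20 − 9 = 11 | 10 |
| Trait anxiety (3.10.2) | 7 | 7 | 20 − 7 = 13 | 13 |
| Ostomy Adjustment Inventory (3.10.3) | 12 | 12 | not applicable | not stated |

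Only the state key fails. Its two stated counts agree with each other and with the 20 items. If nine were right, both stated counts would be wrong. A dropped list entry needs only one slip, so it is the likelier explanation. The article does not show which item is missing.

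**2. Effect on one patient if ten items are truly inverse and nine are reversed**

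- Fully calm: 19 items score 1 and the unreversed item scores 4, so 19 × 1 + 4 = 23 instead of 20.
- Fully anxious: 19 items score 4 and the unreversed item scores 1, so 19 × 4 + 1 = 77 instead of 80.
- The largest error in one score is 3 points.

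**3. Effect on group means (illustration)**

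Inputs, from section 3.5 (Sample): "36.24 ± 8.15 in the experimental group and 48.16 ± 10.14 in the control group". Assumption: each mean is spread evenly over the 20 items. An item with correct mean X/20 then contributes 5 − X/20, so X becomes (19/20)X + 5 − X/20 = 0.9X + 5.

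- 36.24 becomes 0.9 × 36.24 + 5 = 37.62 (shift +1.38).
- 48.16 becomes 0.9 × 48.16 + 5 = 48.34 (shift +0.18).
- The difference goes from 48.16 − 36.24 = 11.92 to 0.9 × 11.92 = 10.73, a loss of 10%.

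The mapping leaves 50, the scale midpoint, unchanged and pulls everything else towards it by one tenth.

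**4. Effect on SD, standardised effect and power**

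The plan's own figures come first. The pooled SD is √[(8.15² + 10.14²)/2] = 9.20, and d = 11.92/9.20 = 1.296 (stated: 1.29). The normal-approximation sample-size formula at d = 1.29 and power 0.99 gives 23 per group, which agrees with "the minimum required sample size was calculated as 46 participants, with 23 participants in each group". The exact noncentral t power at 23 per group is 0.990. Inflation gives 46/(1 − 0.10) = 51.1, rounded up to 52. The planned size reproduces.

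Now flip one of k = 20 equally informative items, with Cronbach's alpha a of 0.94 to 0.96 as quoted in section 3.10.2:

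- Inter-item correlation: r = a/[k − a(k − 1)], which is 0.439 at 0.94 and 0.545 at 0.96.
- SD ratio: √{[20(1 − r) + 18²r]/[20(1 − r) + 20²r]}, which is 0.906 and 0.904. The SD falls from 9.20 to 8.34 and 8.32.
- The confidence interval for the difference narrows in the same proportion, by about 10%.
- d ratio: 0.9/0.906 = 0.993 and 0.9/0.904 ≈ 0.995, so d is 1.287 and 1.290 against 1.296.
- Exact power at 23 per group: 0.9895 and 0.9897 against 0.9903.

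Numerator and denominator shrink together, so the test hardly moves.

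**The case against.** The strongest reply is that this is a typing slip in a journal article about an established instrument. The team will presumably score from the instrument's own key, for which the article cites a Turkish validation study. Other statements in the same section also warn against literal nine-item scoring: the two counts of ten, and the remark that inverse items express positive emotions, which lets each item's direction be read from its wording. The scoring syntax is not shown, and nothing says that it will be copied from this sentence. All of that stands, and it makes the harm conditional. It does not remove the contradiction, which nothing elsewhere in the article repairs.

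Three stronger readings are tempting, and the documents do not support them.

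- **Bias between arms.** A reader might infer this from the unequal shifts of +1.38 and +0.18. The same key would apply to both arms and both time points. The gap between the shifts (1.376 − 0.184 = 1.192, or 10% of 11.92) is the uniform compression seen at two different means, not a second error.
- **Loss of power or a faulty sample size.** The planned size reproduces, and the standardised effect falls by less than 1%.
- **A broken comparison with the planning means.** Those means serve only to derive d. No planned analysis compares trial scores with them, and section 3.5 describes their source as a study of postoperative anxiety, whereas this trial measures anxiety before surgery.

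**Conclusion.** The point holds: the printed key for the primary outcome contradicts its own count, nine listed against ten stated. That the list is at fault, and not the count, is an inference from 10 + 10 = 20. It is a strong one, but the article does not prove it.

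The consequence arises only if the printed list is what gets coded. In that case the fully calm and fully anxious scores become 23 and 77, and raw differences and their confidence intervals shrink by about 10%. The figure of 10.73 points against 11.92 is an illustration. It rests on equally informative items and on the trial reproducing the planning means. The group, time and interaction tests, the standardised effect, the power and the sample size are practically unaffected.

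A reader should not infer that the trial will in fact be mis-scored, or that its primary hypothesis test is compromised. Severity is minor to moderate: an error in an endpoint definition, to be corrected before data collection.

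**What to change.** Check the state-anxiety list in section 3.10.2 against the validated Turkish key that the protocol cites, and insert the missing item number. Take the item from that key and not from inference. If the key turns out to have nine inverse items, correct both stated counts instead.

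Then test the SPSS scoring syntax on two artificial response sets: an all-calm set must return 20 and an all-anxious set 80. A result of 23 or 77 shows that an item is still unreversed.

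The cost is one number in the text and, if the printed list was coded, one line of syntax. Section 3.1 plans recruitment from January 2, 2027, so both can be settled before the first patient is assessed.
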